***Eligibility Requirements***

All MIRA seroconverters are eligible for SOC services. HIV testing is done at every quarterly scheduled visit in the MIRA trial. HIV status is confirmed by ELISA, or other tests as needed, after a participant receives two positive rapid HIV test results.

***Duration of Services***

SOC services are available to a MIRA participant as soon as she seroconverts. Women may participate in the SOC services throughout the life of the MIRA trial, currently scheduled to end in May 2007. SOC services may be accessed while the woman is still active in the MIRA trial and may continue after she completes her participation in the main trial activities and exits the study. Before the trial ends (out of the field in May 2007), study staff will ensure to the greatest extent possible that seroconverters are enrolled or networked into a system of care independent of MIRA. Once the MIRA trial ends, it will not be able to continue to provide payment for HIV-related care or services.

***Services Offered***

In addition to the counseling and health services provided during their participation in the MIRA trial, all MIRA seroconverters are eligible for Standard of Care (SOC) services until the end of the MIRA Trial (approximately May 2007).

The SOC package includes the following four components, which are explained further in the sections below:

1. Psychosocial support and counseling
2. Monitoring of disease progression using CD4 counts
3. Screening for opportunistic infections
4. Access to ARV therapy.
5. **Psychosocial Support Services and Counseling**

Women who seroconvert during the trial have special psychosocial needs. Two to three follow-up post-test counseling sessions are scheduled with HIV-positive participants when their seroconversion is confirmed, depending on participant need. Regular counseling sessions then occur every three months as part of participants’ scheduled MIRA visits. After their participation in MIRA ends, ongoing counseling opportunities with MIRA staff will be available every three months, or sooner if needed. SOC participants also may wish to receive additional psychosocial support beyond the counseling provided at the MIRA clinics, which will be encouraged and facilitated by MIRA staff. Such support may include referrals to one-on-one therapy, support groups, legal aid, health/nutrition information, advocacy, and more. MIRA staff will give SOC participants referral letters to assist them in accessing these local resources.

1. **Monitoring of disease progression using CD4 counts**

Because the study sites have access to different local resources, the two South African sites will rely primarily on referrals for care while the Zimbabwe site will do some procedures at the study clinic in addition to using referrals for other care.

For monitoring disease progression, CD4 counts will be the standard among all three sites. However, some sites will have the ability to run other tests as part of the care given through government and organizational programs. UZ-UCSF is able to perform CD4 counts, full blood counts (FBC), urea & electrolyte (U&E) and a liver function test (LFT) on specimens collected at the MIRA clinic. If a participant consents to the additional procedures in the SOC package, the first testing should occur as soon after seroconversion as possible, CD4 and full blood counts should be repeated every six months, and the U&E and/or LFT may be repeated, as necessary. MRC will perform CD4 tests, and other HIV-monitoring tests, as necessary, at the MIRA clinics upon consenting to the SOC package, and every six-months thereafter, until the participant closes out of the MIRA trial. After the trial, MRC will offer CD4 testing through MIRA labs or at referral sites. PHRU will refer participants for CD4 testing and other HIV-monitoring tests, as necessary, which will be repeated every six months until the end of the MIRA trial.

1. **Opportunistic Infection Screening and Treatment**

While women are still actively participating in the MIRA trial, they will continue to receive physical exams as needed and during their closing MIRA visit. Per MIRA protocol, free treatment for any reproductive or urinary tract infections will be provided. After exiting the MIRA trial, UZ-UCSF SOC participants will continue to be tested and treated (as needed) for Chlamydia, gonorrhea, trichomoniasis and syphilis every six months at the study clinic. After their participation ends in the main trial activities, participants at the MRC and PHRU sites will be referred for all clinical care and testing.

SOC participants at all sites will be referred to outside facilities for opportunistic infection (OI) screening. At the OI clinics, participants will receive physical exams, including screening for anemia, TB (chest X-rays and sputum examinations, if medically indicated), pneumonia, and any other clinical conditions requiring attention. Treatment will be initiated if appropriate. MIRA referral letters will be given to the participant to facilitate the transition to these outside facilities.

1. **Anti-Retroviral (ARV) Therapy**

SOC participants will be referred to governmental or other organizations and/or research studies that provide anti-retroviral (ARV) therapy when they seroconvert. If pregnant, women will also be referred to organizations or clinics providing ARV therapy for prevention of mother-to-child transmission. If a woman becomes eligible for ARV therapy but does not have access to treatment due to waiting lists at local programs, she may be evaluated and seek assistance and treatment through the resources of the MIRA trial until she is accepted into a local program and while the MIRA trial is still ongoing.

Participants will be evaluated by qualified clinicians working in the OI and other referral clinics to determine if they are eligible to begin ARV treatment. This clinical evaluation, combined with the results of laboratory tests, will be used to determine whether the participant should initiate ARVs, per national guidelines.

1. **Guidelines for Initiating ARV Therapy in Zimbabwe**

WHO guidelines for ARV therapy[[3]](#endnote-2)[[4]](#endnote-3) recommend that adults begin ARV therapy when they meet one of the following conditions:

1. Clinically advanced HIV disease defined by:
   1. WHO stage IV HIV disease, irrespective of CD4 cell count, or
   2. WHO stage III disease with a CD4 count <350/mm3
2. WHO stage I or II HIV disease with CD4 counts <200/mm3

Definitions of WHO stages of HIV disease may be found in the Appendix.

1. **Guidelines for Initiating ARV Therapy in South Africa**

In 2004, South Africa’s National Department of Health established national antiretroviral treatment guidelines.[[5]](#endnote-4) Under these guidelines, persons identified as HIV-positive will receive prevention counseling; screening and treatment of TB and other OIs; screening for pregnancy; introduction to HIV services; and CD4 counts to determine disease stage based on WHO criteria. Those in WHO stage I and II will also receive nutrition and psychosocial support.

Initiation of ARV therapy for adults are recommended under the following conditions:

1. CD4 counts <200/mm3, irrespective of HIV disease stage; or
2. WHO stage IV HIV disease, irrespective of CD4 counts *and* when the patient expressed the willingness and readiness to adhere to ARV treatment schedules.

Those receiving ARV treatment will undergo intensive adherence counseling. Palliative care will be sought for those who experience repeated treatment failure.

***Study Sites and Referral Organizations***

1. **Study Sites**

The SOC sites are the same as the MIRA trial sites: The Medical Research Council (MRC), with sites in Umkomaas and Botha’s Hill regions outside Durban, South Africa; Perinatal HIV Research Unit (PHRU), which is based at the Chris Hani Baragwanath Hospital in Johannesburg, South Africa; and the UZ-UCSF Collaborative Research Programme, with MIRA clinics in Chitungwiza and Epworth areas outside Harare, Zimbabwe.

1. **Referral Organizations**
2. **Medical Research Council (MRC)**

MRC has a large network of partner facilities around Durban, South Africa, that will act as referral organizations for SOC participants. In central Durban, McCord Hospital includes two clinics for voluntary counseling and testing (VCT) and screening. Provincial facilities include:

- Addington Hospital, which has an HIV and AIDS resource center (including a VCT clinic), a prevention of mother-to-child transmission (PMTCT) program, and an ARV clinic.
- CJ Crookes Hospital, which has an HIV Clinic, VCT clinic, and an ARV clinic.
- Prince Mshiyeni Hospital (Umlazi), which has an HIV clinic, VCT clinic, and PMTCT clinic.
- R K Khan Hospital, which has an HIV clinic and VCT clinic.
- The Valley Trust, one of South Africa’s oldest and best-known NGOs.
- St. Mary's Hospital, a Catholic Mission Hospital.

For psychosocial support referrals, MRC has partnered with local non-government organizations (NGOs), community-based organizations (CBOs), and other HIV prevention organizations, including McCord’s Sinikithemba Support Group, to build an ongoing psychosocial care support for SOC participants.

1. **Perinatal HIV Research Unit (PHRU)**

The MIRA site of the Perinatal HIV Research Unit (PHRU) is located at the Witswatersrand Academic Hospital, the Chris Hani Baragwanath (CHB) Hospital, in Soweto, Johannesburg. CHB was part of the first wave of government ARV rollout sites in South Africa, and is a PEPFAR recipient. Different sections of this large facility will serve as referral sites for opportunistic infections and ARV therapy.

HIVSA, PHRU’s sister organization, is the NGO providing the psychosocial peer support for the site’s SOC participants. A registered non-profit organization set up to provide support to the women, men and children who are currently or were participating in the PHRU research activities, HIVSA includes services in VCT, wellness, TB treatment, ARV for adults and children, and palliative care run as operational research.

1. **UZ-UCSF Collaborative Research Programme**

Three local opportunistic infection (OI) clinics will be utilized by the UZ-UCSF MIRA site: Parirenyatwa Hospital, operated by the Department of Medicine at the University of Zimbabwe Medical School; Harare Central Hospital in Harare; and Chitungwiza General Hospital, located in a peri-urban suburb 30 km south of Harare.

The UZ-UCSF Programme networks with a variety of support organizations in Harare and in the research communities. The MIRA Senior Counselor has evaluated these organizations and maintains current contact information for each.

***Study Procedures***

1. **Scheduled Visit Summary**

SOC visits initially work in tandem with main MIRA trial visits, and then add additional visits to accommodate the special needs of seroconverters and to continue the participant’s access to services after closing out of MIRA. Seroconverters who have already exited the study will be contacted and asked to return to the clinic to be given the opportunity to participate in SOC services.

There are five types of scheduled visits that SOC participants will experience, and each is described in more detail in the sections below:

- Seroconversion visit
- 2-week confirmatory test results/supportive counseling visit
- MIRA Trial follow-up visit(s)
- Post-trial bi-annual follow-up visit(s)
- Post-trial results notification visit(s)

For each visit described below, only the procedures specifically for seroconverters, or those performed in addition to the regular MIRA trial visits for the SOC, are noted. For the procedures of the regular MIRA quarterly follow-up visits, please see the MIRA Protocol, version 8.0.

1. **Seroconversion Visit**

If a MIRA participant is found to be HIV positive based on her rapid test results at a quarterly

follow-up visit, she will receive immediate post-test counseling. Confirmatory tests will be requested from the laboratory, and the participant will be scheduled for a visit to receive her results approximately 1-2 weeks from the date of the seroconversion visit. At the seroconversion visit, the counselors will give an introduction to the SOC services but will provide further details at her next visit, after her confirmatory results return.

1. **2-week Confirmatory Test Results/ Supportive Counseling Visit**

At this visit, the participant will learn the results of her ELISA confirmatory HIV tests and receive supportive counseling. This visit also provides the opportunity to explain the services, including the SOC, available to the participant at a time where she may be more capable of comprehending her options. If the participant misses this visit, staff will follow MIRA outreach guidelines, which begin by sending her a reminder letter. This letter will not disclose her status or in any way identify her as a seroconverter. A further supportive counseling visit may be scheduled if the counselor feels it is appropriate for the participant.

If a participant is confirmed as HIV-positive, the participant will receive ample post-test counseling and information about positive living, HIV transmission, diet/nutrition, and other relevant topics. The counselor will ask the participant if she would like to hear about the SOC services at this time and if so, will review with her with the SOC Information Sheet. The counselor will ensure that the participant understands the information and that the MIRA trial can only provide these health services, including ARV treatment (if needed), at no cost to her through the end of the MIRA trial (approximately May 2007). Study staff will help every seroconverter to establish a network of care independent of MIRA before the trial ends.

Written Informed Consent: If the participant is interested in taking part of the SOC services, the SOC written informed consent form will be administered. The counselor will explain that we seek her consent for the following procedures:

- Blood and urine specimen collection for performing CD4 and full blood counts, urea and electrolyte (U&E) and liver function tests (LFT).
- STI and pregnancy testing at post-trial bi-annual follow-up visits (or more frequently, if needed), Pap smears on an annual basis, and physical exams, only if clinically indicated. The results of these will be tracked in the participant’s file and used to monitor her health.
- Recording lab results from the above tests, and results from other clinics, in the participant’s MIRA file with her MIRA ID, and no other identifying information.
- Review of medical records from outside organizations.

Staff will remind her that she can still access SOC services, including referral services, without signing the informed consent. The participant will have an option to consent or not to having specimens taken for HIV-monitoring tests mentioned above. She will also have the option to consent or not to having test results recorded for study purposes. Finally, she will have the option to allow the MIRA staff to contact her family to request medical records and hospital notes, in the event of her death.

Once the participant is aware of the referral services available to her, she should be told about the additional counseling and support services outside of the MIRA clinic. Referral letters will be provided to assist her in accessing these services if she is interested.

1. **MIRA Trial Follow-up Visit(s)**

The participant should continue her scheduled MIRA Trial follow-up visits unless she or a clinician decides to discontinue her from the study. Counseling the participant about positive living is the centerpiece of every seroconverter’s follow-up visit. Positive pregnancy results will be given with full explanation of the options available to her in her community, including prevention of mother-to-child transmission services. Positive STI results will be disclosed with a thorough explanation of the heightened risk of transmission associated with STIs.

If a seroconversion is identified, and a participant consents to additional lab testing, specimen collection should be arranged as soon as possible. This may be at the supportive counseling visit, at an unscheduled visit, or at the next regularly scheduled visit. Specimen collection for CD4 counts will be performed at study clinics or by referral organization, depending on site specifications.

1. **Post-trial Bi-annual Follow-up Visit(s)**

The purpose of the bi-annual follow-up visit (or more frequent as needed) is to 1) offer supportive counseling to the participant and her partner (if requested); 2) collect specimen for CD4 counts and other blood and urine tests to monitor the participant’s disease progression; 3) test for pregnancy and sexually transmitted infections; and 4) offer referral for OI screening; 5) offer referrals to other services as needed. Women will only receive a pelvic exam at a follow-up visit when it is clinically indicated.

Bi-annual follow-up visits will occur at the MIRA clinic at UZ-UCSF, and at referral organizations at MRC and PHRU. The MIRA team proposes to implement an invoicing system to track general utilization of referral services.

If the participant misses a scheduled bi-annual follow-up visit, staff may send a reminder letter that will not disclose her status or in any way identify her as a seroconverter. However, there is no requirement to do home visits or track her as during the study.

1. **Results Notification Visit(s)**

Participants who provide blood and urine samples for testing will be scheduled for a results notification visit 1-2 weeks later. At this visit, test results, including HIV monitoring indicators, should be explained to the participant. Post-test counseling, if needed, will be provided, as will treatment if RTI/STI positive. If the participant misses a scheduled results notification visit, staff should send a reminder letter. This letter should not disclose her status or in any way identify her as a seroconverter.

***Data Collection, Management, and Analysis***

1. **Data Collection and Analysis**

Since the SOC is fundamentally a service package and not a research study, data collection is not its primary purpose. However, sites are seeking IRB and participant approval to collect minimal data (e.g., surveillance data) that is obtained in the process of providing care. CD4 and full blood count, as well as U&E and LFT, results will be recorded when they are completed if the participant has granted consent for data collection. In addition, STI, pregnancy and Pap smear data will be recorded. Frequencies of referrals given to participants and utilized will be recorded by each clinic so that the uptake of services may be reported to the funder. We propose to do a descriptive analysis on baseline CD4 counts at seroconversion and rate of disease progression (timing to qualifying for ARV therapy).

1. **Case Report Forms (CRFs) and Source Documents**

The MIRA Standard of Care SOC Form is the only CRF used in the SOC. This form will record the results of blood and urine tests, as well as Pap smear results, and will be transmitted via DataFax to UCSF’s Center for International Data Evaluation and Analysis (CIDEA). With the participant’s consent, test results from outside facilities will also be recorded on the CRF. If a participant does not provide consent for data collection, test results will be indicated on chart notes only, and no results will be collected on the CRF. Referrals will be tracked on a log in each SOC participant’s binder. Draft examples of each of these documents can be found in the Appendix.

1. **Referral Letters**

MIRA clinics will develop referral letters that will facilitate participants’ transitions to outside services. Depending on the requirements of different agencies, the referral letters may contain the participant’s name, National ID number and the date when it was issued by the MIRA trial, but will not include her MIRA ID number. The letter will feature a perforated bottom section that the referral organization will tear off and return to the MIRA clinic. This slip will indicate that a service was used at the organization and it will not include participant names, MIRA ID numbers or health information.

Please note that if an organization requires proof of HIV status and/or other lab results, the participant will be given these results separately from her referral letter to deliver to the organization.

***Human Subjects Consideration***

1. **Institutional Review Board (IRB) Review**

We will seek approval of this protocol from the Committee on Human Research at UCSF prior to commencing any procedure described herein. We will ensure that all procedures conform to U.S., South African and Zimbabwean ethical standards regarding research involving human subjects.

1. **Informed Consent**

Eligible MIRA Trial participants who accept the SOC services will be asked to review and sign a site-specific informed consent in the presence of a MIRA staff member and a witness. Since each site is approaching in-house procedures, referral services, and data collection in a unique way, the informed consent will differ according to the sites activities.

1. **Compensation**

Participant compensation for completing regularly scheduled MIRA visits remains as defined in the MIRA Protocol, version 8.0. Seroconverters who accept SOC services will receive transport reimbursement for attending any scheduled SOC visit at the MIRA clinic after discontinuation from the Main Study, which are as follows:

- Bi-annual follow-up visit (s)
- Results notification visit (s)

A transport reimbursement amount in local currency will be adjusted regularly to reflect the current equivalent value of not more than US$5. Unscheduled or interim visits, or visits to off-site referral agencies, are not eligible for transport reimbursement. Site managers may approve exceptions to this reimbursement policy on a case-by-case basis, as needed.

1. **Payment for Services**

The MIRA trial will pay for all SOC services, including ARV treatment (if needed), until the MIRA trial ends (approximately May 2007).

1. **Benefits and Risks**

This care package offers numerous benefits. Through these services, MIRA staff will help to monitor participants’ health, HIV infection, and emotional wellbeing. Participants’ disease progression will be tracked through CD4 counts and other blood and urine tests. Participants will be referred to services and treatment studies available in their community, including opportunistic infection screening and treatment and ARV therapy, if they become eligible. If the participant is or becomes pregnant, she will be referred to organizations that provide ARV therapy to help prevent maternal-to-child HIV transmission. Numerous counseling and other psychosocial support services will be offered to participants to help them adjust to life as an HIV-positive individual.

While the study staff will ensure participants’ confidentiality at the clinic, it is possible that other people may discover SOC participants’ HIV status if they find out that they are participating in this care package. Also, the care package as described here will no longer be available after the MIRA Trial ends—currently scheduled for May 2007. However, our goal is to connect participants with the best care and services available in their area so that they will already have an established relationship with local resources when the study ends.

***Specimen Storage***

Study specimens will not be stored. All specimens will be destroyed after receiving confirmed test results.

## Protocol for Prostate-Specific Antigen (PSA) Ancillary Study

*Version 3.0, May 10, 2007*

***Study name: Audio computer-assisted self-interviewing (ACASI) vs. face-to-face (FTF) interviewing – a randomized comparison using prostate specific antigen (PSA)***

**Sub-study objectives:** To compare the validity of reports on sexual behaviors obtained using two interview modes (ACASI and FTF) using prostate-specific antigen (PSA) as a biomarker for unprotected intercourse.

Specifically, we will compare the proportion of women in the two groups (ACASI and FTF) who are PSA-positive but report they have not engaged in unprotected intercourse (i.e. intercourse without a condom) in the past 48 hours.

**Research justification:** This study will document which of two approaches of asking participants sensitive questions about their recent sexual activity provides more valid responses. Valid information about sexual activity, more generally, is necessary for the interpretation of clinical trial results.

These findings will provide an assessment of the accuracy of self-reported recent sexual activity and condom use among women who exited the MIRA trial. It may inform the design of future studies that require accurate information on recent sexual behavior and provide guidance about the contribution of ACASI to increased accuracy in self-reports.

**Research methods (including recruitment plan):** Women who complete the MIRA study at the Zimbabwe site will be eligible to return to the clinic and complete the additional procedures required for this ancillary study, which will be conducted beginning in December 2006 after all of the scheduled MIRA closing visits have taken place

With a two-arm, randomized design, we will compare discordance between FTF and PSA with the discordance between ACASI and PSA. Half the participants will complete their interview FTF and the other half will complete an ACASI questionnaire. The questionnaire will assess sexual activity and method use during the previous few days, as well as product use, generally, since completion of the MIRA trial.

The desired sample size of 1,000 women could be achieved in several ways : 1) MIRA study participants are notified about the PSA study (verbally and/or with a flyer) at their closing visit for MIRA; 2) women are scheduled for the PSA study visit at their final MIRA trial visit; 3) MIRA study participants are actively recruited for the PSA study through community outreach activities that would target MIRA participants who have exited the trial; and 4) MIRA participants who return to the clinic for an additional supply of products are recruited to participate in the PSA study. With a sample size of approximately 1,000 women we would have about 80% power to detect a 30% reduction in discordance, assuming the discordance in the FTF group is 20% (one-sided test; alpha 0.05).

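### The PSA sub-study compares interview modes on a proportion of all women, although only PSA-positive women can be discordant; a comparison among PSA-positive women would be more powerful and would match a conclusion about under-reporting

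*Protocol*

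**What the plan says.** Appendix 16.6 randomises women leaving the trial at the Zimbabwe site to audio computer-assisted self-interview (ACASI) or face-to-face (FTF) interview, and tests a self-collected vaginal swab for PSA as a marker of unprotected intercourse.

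- **Outcome** (Sub-study objectives): "compare the proportion of women in the two groups (ACASI and FTF) who are PSA-positive but report they have not engaged in unprotected intercourse". The recall period is 48 hours. The numerator is one cell of the report-by-PSA table, and the denominator is all women in the mode.
- **Purpose** (Research justification): "This study will document which of two approaches of asking participants sensitive questions about their recent sexual activity provides more valid responses".
- **Allocation** (Research methods): "Half the participants will complete their interview FTF and the other half will complete an ACASI questionnaire".
- **Power** (Research methods): "With a sample size of approximately 1,000 women we would have about 80% power to detect a 30% reduction in discordance". The discordance assumed for the FTF group is 20%, and the test is given as "one-sided test; alpha 0.05". The sentence does not say what the 20% is a share of.

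The appendix gives no expected share of PSA-positive women. It describes no analysis restricted to PSA-positive women and no measure of over-reporting. The Research methods paragraph also speaks of discordance between report and PSA without giving a direction.

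**The concern.** Two features of the endpoint deserve attention.

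First, the denominator. Discordance is defined as a positive PSA test together with a denial, so PSA-negative women count as concordant whatever they say. They carry no information on how honestly exposed women answer. They do bring in the chance imbalance between modes in the number of PSA-positive women, which has nothing to do with interview mode.

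Second, the scope. The endpoint measures denial by women with evidence of exposure. The justification promises a statement about validity in general, which also depends on what women without evidence of exposure report.

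At stake are the precision of the sub-study and the wording of its conclusion. The HIV result of the main trial is not affected.

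**Working it through.** **Inputs.** From Appendix 16.6: about 1,000 women, half per mode (n = 500); FTF discordance 20%; a 30% relative reduction, so ACASI discordance is 0.20 × 0.70 = 14%; one-sided alpha 0.05. Assumed, because the protocol is silent: the PSA-positive share q, taken from 30% to 80%.

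**Step 1: reproduce the stated power.** For proportions p1 and p2 with n per mode and mean p̄,

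z = [ (p1 − p2) − 1.645 × √(2p̄(1 − p̄)/n) ] / √( (p1(1 − p1) + p2(1 − p2))/n ), and power = Φ(z).

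With 0.20, 0.14 and n = 500, p̄ = 0.17. The pooled standard error is √(0.2822/500) = 0.02376 and the unpooled one is √(0.2804/500) = 0.02368. So z = (0.06 − 0.03908)/0.02368 = 0.88, and power = 81%. The stated figure of about 80% is reproduced, with all 1,000 women in the denominator and a one-sided test. The two-sided version gives 71.5% and does not match.

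**Step 2: where the efficiency goes.** Let d be the proportion of PSA-positive women who deny unprotected intercourse, so that the all-women proportion is qd. Its variance splits into two parts:

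qd(1 − qd)/n = qd(1 − d)/n + d²q(1 − q)/n.

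The first term is the variation in denial among PSA-positive women. The second is d² times the variance of the observed PSA-positive share, and it is pure noise for this question. In the FTF mode at q = 0.4 and d = 0.5, 0.00032 = 0.00020 + 0.00012.

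**Step 3: restrict to PSA-positive women.** The same 20% v 14% of all women become denial rates 0.20/q v 0.14/q, with 500q women per mode. At q = 0.4 this is 50% v 35% with 200 per mode. Then p̄ = 0.425, the pooled standard error is √(0.48875/200) = 0.04943 and the unpooled one is √(0.4775/200) = 0.04886. So z = (0.15 − 0.08131)/0.04886 = 1.41, and power = 92%.

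| PSA-positive share (assumed) | PSA-positive women per mode | Denial, FTF v ACASI | Power among PSA-positive women | Power, all women |
|---|---|---|---|---|
| 30% | 150 | 66.7% v 46.7% | 97% | 81% |
| 40% | 200 | 50% v 35% | 92% | 81% |
| 50% | 250 | 40% v 28% | 88% | 81% |
| 60% | 300 | 33.3% v 23.3% | 86% | 81% |
| 80% | 400 | 25% v 17.5% | 83% | 81% |

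A simulation with random PSA-positive counts (200,000 runs) agreed within about one percentage point.

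**Step 4: is the restricted comparison still randomised?** PSA reflects intercourse before the visit, and the mode is assigned at the visit. The mode cannot change PSA status, so PSA-positive women in the two modes remain comparable by randomisation.

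**Step 5: an implied condition.** Discordance of 20% of all women is possible only if at least 20% of all women are PSA-positive. The power sentence rests on this without saying so.

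**The case against.** The strongest reply is that nothing stated is wrong. The power figure reproduces. Because mode is randomised, the PSA-positive share is equal in expectation, so the all-women comparison is an unbiased test of under-reporting. That is the error ACASI is meant to reduce: Section 8.5 says it increases reporting of sensitive behaviours. All of this stands, and the point is one of efficiency and scope.

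The size of the gain also rests on a share the protocol does not give. The 97% at a 30% share requires two-thirds of PSA-positive FTF women to deny exposure, and at an 80% share the gain is about two points. This limits the size, but the direction is the same at every share examined.

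A reader might infer that the sub-study cannot show which mode is more valid. The documents do not support that. As an illustration, take q = 0.4, denial of 50% v 35%, and over-reporting by 5% of PSA-negative FTF women. Total FTF mismatch is 0.4 × 0.50 + 0.6 × 0.05 = 23%. ACASI mismatch is 0.4 × 0.35 + 0.6 × 0.05 = 17% with equal over-reporting, and it reaches 23% only when its over-reporting is 15%. The ranking reverses only if ACASI over-reporting exceeds FTF over-reporting by more than 10 points, and nothing in the protocol suggests that. Nor does the protocol exclude tabulating PSA-negative women, since every participant is to give both an interview and a swab.

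**Conclusion.** The endpoint is valid and adequately powered as defined, but its denominator is inefficient and its scope is narrower than the stated aim. On the protocol's own 20% v 14%, comparing denial among PSA-positive women raises power from 81% to between 83% and 97% for PSA-positive shares from 80% down to 30%. It also gives a quantity that is easier to interpret: the share of women with evidence of exposure who deny it. The gain rests on the assumed share. The comparability of the modes rests on PSA status being fixed before the interview.

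Two stronger readings should not be drawn. One is that the sub-study is underpowered because the 20% is a share of PSA-positive women. Power on that reading would be about 40% to 73% for shares of 30% to 80%, but the written outcome and the reproduced 80% both point to all women. The other is that a mode should be called more valid only if it does not raise positive answers among PSA-negative women. That assumes PSA misses no true exposure, and the protocol gives no sensitivity or detection window for the test. A more honest mode could be penalised by such a rule.

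**What to change.** 1. Define the primary comparison as the proportion of PSA-positive women who report no unprotected intercourse in the past 48 hours, by randomised interview mode. The all-women proportion can stay as a supporting result.
2. In the power sentence, say that the 20% is a share of all women, give the assumed PSA-positive share, and show power over a range of that share.
3. Limit the conclusion to under-reporting of unprotected intercourse.
4. Tabulate PSA-negative women's answers by mode descriptively, and do not use them as a decision rule.

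The cost is a change to the outcome and power wording. No extra women, swabs or interviews are needed. The one downside is that the number analysed is the PSA-positive count, which is not known in advance.
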